### Blinding

A physiotherapist (independent from the investigator) performed the baseline assessments for all the older participants (before allocation) during the first week. Then, an independent member of the team allocated the participants to different groups using a random number generator and informed the main investigator. The second assessment in week 6 was performed by another physiotherapist or physician (different from the initial one who performed the baseline measurements). The third and final assessment at week 12 was performed by another physiotherapist or physician who was not familiar with the previous assessments. While we attempted to maintain blinding at follow-up, this was not possible. Double blinding was not possible, as the participants knew whether they were exercising using the MIRA Rehab system. It was not possible to blind the medical team and the participants because the participants received rehabilitation sessions as part of their daily routines.

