### Outcome Measures

This feasibility study included all the quantitative and qualitative outcome measures we anticipate, including in the future RCT, to inform the design of the main study. The outcome measures were assessed for their suitability for the main trial. These were assessed in terms of practicality (ie, recruitment rates, attrition rates, and eligibility criteria), data collection methods, required resources, and adherence (see Textbox 2).

Other variables of interest for this trial were as follows: (1) balance (measured by the Berg Balance Scale) [31]; (2) functional ability (balance, functional ability, and mobility measured by the Timed Up and Go test) [32]; (3) outcomes on the Functional Reach Test [33,34]; (4) the Short Physical Performance Battery [35]; (5) fear of falling (measured with the Fall Efficacy Scale–International) [36]; (6) depression (measured using the Geriatric Depression Scale) [37]; (7) quality of life (measured using the EQ-5D-5L) [38]; (8) exercise adherence (measured through the MIRA Rehab platform); and (9) usability and acceptability (measured using the System Usability Scale and the Technology Assessment Model) [39]. We also collected qualitative structured interview data from the participants who were asked to describe their experiences, including what they liked (facilitators) and disliked (barriers), to help us understand the success (or otherwise) of the intervention (Multimedia Appendix 4 and Table 1).

Feasibility outcomes.

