### Statistical Analysis

Statistical analysis is currently underway. The baseline characteristics of the participants will be reported using mean and SD values for normally distributed variables and median and IQR values ranges for nonnormally distributed variables. Analysis is being conducted using SPSS (version 27.0; IBM Corp) [40]. Continuous data, such as retention and recruitment rates, will be identified as percentages. Both groups will be compared at baseline with respect to their continuous and categorical variables using independent samples *t* tests and the Fisher exact test, respectively. Changes in balance and function will be compared between the intervention group and the control group from baseline (week 0) to follow-up (weeks 6 and 12). Inferential findings will be interpreted cautiously, as the feasibility analysis is underpowered for detecting significant effects. Distribution of data will be explored as normal or skewed. For normal distributions, mean and SDs will be used. For skewed distributions, minima, maxima, medians, and quartiles will also be used. We will report 95% CIs for unadjusted differences in mean outcome scores between the groups. Changes in mean scores over 3 time points (weeks 0, 6, and 12) as well as changes in average scores for each result will be recorded using repeated measures ANOVA. The effect size for the differences between the intervention and control groups and the variations within the intervention group will be estimated. Other relevant models will be used in the case of nonnormally distributed data. The findings will be used to calculate the optimum sample size (number of participants) for determining a statistically significant true effect in preparation of a future definitive RCT. Both intention-to-treat and per-protocol analyses will be undertaken. This feasibility RCT is a hypothesis-generating study for preparing and conducting additional analyses not identified in this protocol paper.

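### Each visit has a different assessor, so the planned time effect and within-intervention effect size cannot be separated from rater differences on the staff-administered tests

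*Protocol article*

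**What the plan says.** The Blinding section ties the assessor to the visit.

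- Week 0: "A physiotherapist (independent from the investigator) performed the baseline assessments for all the older participants (before allocation) during the first week".
- Week 6: "The second assessment in week 6 was performed by another physiotherapist or physician (different from the initial one who performed the baseline measurements".
- Week 12: "The third and final assessment at week 12 was performed by another physiotherapist or physician who was not familiar with the previous assessments".

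The same section concedes that blinding at follow-up was attempted but could not be kept.

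Table 1 schedules the Berg Balance Scale, Timed Up and Go, Functional Reach Test and Short Physical Performance Battery at all three visits.

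The Statistical Analysis section compares change in balance and function between the arms, with 95% confidence intervals for unadjusted differences in means. It also commits to two analyses of change over time. Scores at the three time points and "changes in average scores for each result will be recorded using repeated measures ANOVA". In addition, "The effect size for the differences between the intervention and control groups and the variations within the intervention group will be estimated". The findings are then to be used to calculate the sample size of a definitive trial, with no restriction to between-arm estimates.

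**The concern.** A before-after comparison attributes the difference between two visits to time. Here the person scoring or timing the test changes at the same moment. If the week 6 assessor is more generous on the Berg items than the baseline assessor, or starts and stops the clock differently on the Timed Up and Go, the whole sample appears to improve or decline. Nothing in the data can say which explanation is right.

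Two planned results are exposed: the time main effect of the ANOVA and the effect size within the intervention group. Both could be reported as preliminary signs of benefit. The within-arm effect size could also be carried into the sample size of the definitive trial, which is a stated purpose of this study. An effect size that contains a rater shift would then mislead the next design. More participants would not help, because the problem is bias and not imprecision.

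**Working it through.** **1. The plan's own sample size.** The Sample Size section aims for about 15 per arm after 20% attrition. 15 / (1 − 0.20) = 18.75, rounded up to 19 per arm and 38 in total. This reproduces. The evaluable numbers used below are therefore 15 per arm and 30 in all.

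**2. Can time and assessor be separated?** Write a model with an intercept, group, two time indicators (weeks 6 and 12), two assessor indicators (second and third assessor) and two group-by-time terms. That is 8 columns. With one assessor per visit, each assessor column is identical to a time column, so the rank is 6. Without the assessor columns the model has 6 columns and rank 6. No analysis model can recover the lost information. This step needs no assumed number.

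**3. How large could the artefact be?** Assumptions, none of them in the article:

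- no true change;
- a constant rater shift of b SD between baseline and one follow-up visit;
- correlation r between visits of 0.5 to 0.8;
- a two-sided 5% test of that single contrast.

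Formulas, in units of the outcome SD:

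- SD of change = √(2(1 − r)), which is 1.000 at r = 0.5 and 0.632 at r = 0.8.
- Apparent standardised change dz = b / √(2(1 − r)).
- Probability of a significant result: non-central t with n − 1 degrees of freedom and non-centrality dz·√n.

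Worked case, b = 0.3 and r = 0.8: dz = 0.3 / 0.632 = 0.47. The non-centrality is 0.474 × √15 = 1.84 for one arm and 0.474 × √30 = 2.60 for both arms. The probabilities are 40% and 71%.

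| Shift b | dz, r = 0.5 to 0.8 | Within-arm change significant, n = 15 | Time effect significant, n = 30 |
|---|---|---|---|
| 0.2 SD | 0.20–0.32 | 11–21% | 19–39% |
| 0.3 SD | 0.30–0.47 | 19–40% | 36–71% |
| 0.5 SD | 0.50–0.79 | 44–81% | 75–99% |

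A simulation of 20,000 trials per setting agrees to within about one percentage point. With b = 0 it returns 4.8–5.2% for the within-arm test and 5.0–5.1% for the time effect.

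**4. The between-arm contrast.** If both arms share the assessor at a visit, the difference in mean change is (true change in the intervention arm + b) − (true change in the control arm + b), and b cancels. In the same simulations the mean between-arm difference was about 0 and the rejection rate 4.8–5.2% at every shift.

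**5. SD and correlation.** Adding a constant b to every follow-up score changes neither: Var(Y₁ + b − Y₀) = Var(Y₁ − Y₀). Only disagreement that varies by participant, or several raters within one visit, would alter them.

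**The case against.** The strongest reply is about weight. The article says that it does not assess effectiveness and that differences between groups are not a key objective. Its feasibility outcomes (recruitment, attrition, resources and adherence) are untouched by who rates the tests. The between-arm comparison is also planned, and it survives. All of this stands, and it keeps the point below a must-fix. It does not remove it, because the within-intervention effect size is an explicit commitment and the study exists to supply parameters for the next trial. The article's caution about inferential findings is tied to low power, which is a different problem from bias.

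A second reply is that a condensed article may leave assessor training and calibration to the full protocol. That is fair. Silence on training is not counted here as a fault, and it gives no support to any particular size of shift. The aliasing follows from what the article does state.

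Third, full aliasing assumes one assessor per visit, which is how the singular wording reads. If several people shared a follow-up visit, the week 6 assessor is still stated to differ from the baseline one and the week 12 assessor reads as new, so change from baseline would still coincide with a change of rater.

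Two stronger readings are tempting. A reader might infer that the randomised comparison is biased too. That would need assessors to be linked to arm, and nothing in the Blinding section suggests it. The admitted failure of blinding at follow-up is a separate matter. A reader might also infer that changing raters necessarily lowers the correlation and inflates the SD of change. Step 5 shows that a constant shift does neither, so the most that can be said is that these quantities may include inter-rater variance.

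**Conclusion.** The point holds for the four staff-administered tests and for two planned results: the ANOVA time main effect and the within-intervention effect size. Neither can be read as change or used to size the definitive trial. The self-report questionnaires (fear of falling, depression, quality of life) are less exposed.

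The identification problem rests only on the article's description of the assessors. Its size is unknown. The illustrative rates depend on assumed shifts and correlations, and the upper end of each range belongs to r = 0.8 alone. The randomised contrast is unbiased by a shift common to both arms. Severity: moderate.

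**What to change.** Data collection is over, so the rotation of assessors cannot be changed, but the article describes the analysis as still underway. In the Statistical Analysis section:

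- Remove the effect size for variation within the intervention group.
- State that the ANOVA time main effect will not be interpreted.
- Report between-arm differences at week 6 and at week 12, each adjusted for the baseline score, with 95% confidence intervals, in place of unadjusted differences. The cancellation of a common shift does not depend on the adjustment; adjusting also deals with chance baseline imbalance in arms of about 15.
- Base the sample size of the definitive trial on between-arm quantities only.
- If assessor identity was recorded, tabulate it by arm at each visit. The article does not say whether it was.
- State as a limitation that SDs of change and correlations between visits may include inter-rater variance.

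The cost is a few lines of wording and, where the data exist, one table. What is lost is a before-after figure that could not be interpreted.

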## Methods

### Study Design

The study was conducted in Saudi Arabia and was a single-center, 2-arm, single-blind, parallel-group feasibility RCT. The reporting of this feasibility RCT followed the Consolidated Standards of Reporting Trials extension for feasibility trials in order to offer a clear report and appraisal [23] (see Multimedia Appendix 1).

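### The trial is labelled single-blind, but its Blinding section shows no party blind to arm at weeks 6 and 12; the label and the reading of assessor-scored differences need correcting

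*Protocol article*

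**What the plan says.** In the protocol article, Study Design states that the trial "was a single-center, 2-arm, single-blind, parallel-group feasibility RCT". It does not name the party that was blind.

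The Blinding section gives the detail:

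- An independent physiotherapist "performed the baseline assessments for all the older participants (before allocation) during the first week".
- A team member then "allocated the participants to different groups using a random number generator and informed the main investigator".
- Week 6 was assessed by a different physiotherapist or physician, and week 12 by yet another, who did not know the earlier assessments.
- On the follow-up visits: "While we attempted to maintain blinding at follow-up, this was not possible".
- On participants: "Double blinding was not possible, as the participants knew whether they were exercising using the MIRA Rehab system".
- On staff and participants together: "It was not possible to blind the medical team and the participants because the participants received rehabilitation sessions as part of their daily routines".

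The section on Statistical Analysis plans between-group comparisons from baseline to weeks 6 and 12, confidence intervals for differences in means, and effect sizes. It says the findings will feed the sample size of a definitive trial. The one caution it gives on inference is lack of power.

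**The concern.** The design label and the account of blinding contradict each other. Both are written in the past tense about the conducted trial, so one is not simply a plan that later events overtook.

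Two things are at stake. First, the label is the phrase that later summaries and the authors of the definitive protocol are likely to carry forward, and for a trial with unblindable participants it is naturally read as assessor-blind. Second, four of the outcomes are scored or timed by the assessor, and their differences at weeks 6 and 12 are among the results meant to inform the next trial. Low power makes those differences imprecise, whereas knowledge of arm can shift them systematically. A caution about power does not cover that.

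Failure to keep assessors blind in a single care home is also something a feasibility study should report. The feasibility outcomes in Textbox 2 do not list it, and Expected Findings mentions only the small sample and the single site researcher as limits of this kind.

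**Working it through.** This is a comparison of texts. The only sample size in the article does not depend on it, and it reproduces: 15 per arm with 20% attrition gives 15 / (1 − 0.20) = 18.75, rounded up to 19 per arm, or 2 × 19 = 38 in total, as stated.

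**Step 1. Who could be the blind party?** Taking each party in turn from the Blinding section:

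| Party | Knowledge of arm after randomization |
|---|---|
| Participants | Knew whether they used the exergames |
| Medical team | Stated as not possible to blind |
| Main investigator | Told the allocation |
| Baseline assessor | Worked before allocation, so there was no arm to know |
| Week 6 assessor | A different person; not stated to be unaware of arm |
| Week 12 assessor | A different person, unfamiliar with earlier assessments; not stated to be unaware of arm |

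Once participants, medical team and investigator are excluded, the outcome assessors are the only candidates left. The sentence on follow-up then removes them for weeks 6 and 12. No party is shown to be blind after randomization.

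**Step 2. What protection remains?** The baseline values were taken before allocation, so knowledge of arm cannot have influenced them. Changing assessors, with the last one unfamiliar with earlier assessments, limits carry-over of earlier scores. Neither measure conceals the arm at follow-up.

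**Step 3. Which outcomes does the failure affect?** Table 1 schedules seven scales or tests at weeks 0, 6 and 12.

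- Assessor-scored or assessor-timed: Berg Balance Scale, Timed Up and Go, Functional Reach Test, Short Physical Performance Battery. Assessor blinding would have protected these.
- Participant-reported: Fall Efficacy Scale–International, Geriatric Depression Scale, EQ-5D-5L. Participants knew their arm, so these would be exposed even with blind assessors. Their exposure does not result from this failure.

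**Step 4. Where do the affected results go?** Statistical Analysis estimates between-group effect sizes and passes the findings to the sample size of the definitive trial. It does not state that the observed difference will be the target effect, and it does not rule that out.

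**Step 5. Can the bias be sized?** No. The article gives no number of assessments made with knowledge of arm, no agreement data between blind and unblind raters, and no outcome data.

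**The case against.** The strongest reply is that nothing is concealed. The Blinding section admits the failure plainly, and Study Design can be read as the intended design with Blinding as the account of conduct. This stands in part. A reader might infer that the article claims a working protection against assessor bias, or that the label hides its absence; the disclosure does not support either reading. It also argues for keeping the intended design visible rather than deleting it. It does not rescue the label, which is stated in the past tense and without qualification.

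The second reply is that little depends on it. Aims and Objectives says effectiveness was not assessed, Sample Size says group differences are not a key objective, and the listed feasibility outcomes are mostly counts and times that an assessor's knowledge of arm hardly touches. This also stands: no confirmatory conclusion falls, and it sets the severity.

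A reader might also infer a numerical consequence, such as an inflated pilot effect leading to an undersized definitive trial by a given amount. The documents do not support that. Any bias in SD units and any true effect would have to be invented, and the article does not say that the next trial will be sized on the observed difference. With about 15 per arm, the standard error of a standardized difference is roughly √(2/15) = 0.37, so sizing on a pilot effect would be unsafe even with perfect blinding. That is a separate problem and adds nothing to the severity here.

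Finally, the Abstract says data collection ended in March 2022, and nothing says that assessors' knowledge of arm was recorded. Counts by arm may not be recoverable, so they cannot be demanded.

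**Conclusion.** The point holds as an error in a stated design property: single-blind does not describe weeks 6 and 12. Its consequence is confined to the four assessor-scored tests, whose between-group differences at follow-up may carry detection bias in addition to low precision. Neither the size nor the direction of that bias can be derived from the article, so no magnitude is claimed.

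The conclusion rests on one inference, that the assessors were the party meant to be blind. Study Design does not say so, and it follows by elimination. It does not rest on every follow-up assessment having been made with knowledge of arm. The article says only that blinding could not be maintained, and it shows no follow-up assessment to have been blind.

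Severity is moderate: the failure is disclosed and the study does not assess effectiveness, but the label is wrong as written and the stated caution on inference addresses only power.

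**What to change.** 1. **Study Design:** replace the single-blind label with wording such as: intended assessor-blind, not maintained; open-label in conduct. This keeps the planned design on record beside what happened.
2. **Feasibility outcomes and results:** report the failure to maintain assessor blinding as a feasibility finding. Give the number of week 6 and week 12 assessments made with knowledge of arm only where this was recorded; otherwise say that it was not.
3. **Statistical Analysis:** add that between-group differences at weeks 6 and 12 on the Berg Balance Scale, Timed Up and Go, Functional Reach Test and Short Physical Performance Battery may carry detection bias as well as being underpowered, and will not be used as the target effect for the definitive trial.

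The cost is a few sentences. No new data are needed, and the article says analysis was still under way. The only downside is that the trial looks slightly less rigorous.

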### Statistical Analysis

Statistical analysis is currently underway. The baseline characteristics of the participants will be reported using mean and SD values for normally distributed variables and median and IQR values ranges for nonnormally distributed variables. Analysis is being conducted using SPSS (version 27.0; IBM Corp) [40]. Continuous data, such as retention and recruitment rates, will be identified as percentages. Both groups will be compared at baseline with respect to their continuous and categorical variables using independent samples *t* tests and the Fisher exact test, respectively. Changes in balance and function will be compared between the intervention group and the control group from baseline (week 0) to follow-up (weeks 6 and 12). Inferential findings will be interpreted cautiously, as the feasibility analysis is underpowered for detecting significant effects. Distribution of data will be explored as normal or skewed. For normal distributions, mean and SDs will be used. For skewed distributions, minima, maxima, medians, and quartiles will also be used. We will report 95% CIs for unadjusted differences in mean outcome scores between the groups. Changes in mean scores over 3 time points (weeks 0, 6, and 12) as well as changes in average scores for each result will be recorded using repeated measures ANOVA. The effect size for the differences between the intervention and control groups and the variations within the intervention group will be estimated. Other relevant models will be used in the case of nonnormally distributed data. The findings will be used to calculate the optimum sample size (number of participants) for determining a statistically significant true effect in preparation of a future definitive RCT. Both intention-to-treat and per-protocol analyses will be undertaken. This feasibility RCT is a hypothesis-generating study for preparing and conducting additional analyses not identified in this protocol paper.

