### Randomization

Randomization to the intervention or control group was undertaken by a separate member of the research team after baseline measurements were taken. We used an equal allocation ratio of 1:1. Taking into account the allocation ratio for 2 groups, the block size can be 2, 4, or 6. Randomization was undertaken by permuted blocks of size 2-6, using the Sealed Envelope randomization service [27].

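### Baseline t tests and Fisher exact tests between the randomised arms say nothing useful about balance and should give way to description; the issue is minor, as no stated decision depends on them

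*Protocol article*

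**What the plan says.** Under Statistical Analysis, the protocol article plans significance tests between the arms at baseline: "Both groups will be compared at baseline with respect to their continuous and categorical variables using independent samples *t* tests". Categorical variables are assigned to Fisher's exact test in the same sentence. The section gives no purpose for these tests, no significance level for them, and no rule that acts on their results.

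The Randomization section fixes the order of events: "Randomization to the intervention or control group was undertaken by a separate member of the research team after baseline measurements were taken". It adds "We used an equal allocation ratio of 1:1" and "Randomization was undertaken by permuted blocks of size 2-6, using the Sealed Envelope randomization service". The Blinding section also places the baseline assessments before allocation.

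The same Statistical Analysis section already plans descriptive baseline summaries (mean and SD, or median and IQR). For outcomes it plans comparisons of change from week 0, a repeated measures ANOVA over the three time points, and this: "We will report 95% CIs for unadjusted differences in mean outcome scores between the groups". It names no baseline covariate.

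**The concern.** A test between arms at baseline has as its null that both arms come from the same population. Random allocation after measurement makes that null true, provided the allocation was carried out properly. A small p-value is then a chance event, and a large one is not evidence that the arms are alike. The useful question is whether the imbalance seen in these 38 men is large, and in a variable that predicts outcome. A p-value answers neither part. It depends on the sample size and takes no account of prognostic strength.

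The results can mislead in two directions. A significant baseline difference may be read as a fault in the randomisation, which would be an unfortunate message from a trial whose purpose is to show whether an RCT can be run. A non-significant one may be reported as showing that the groups were comparable when a sizeable imbalance is present. The general caution in the section, that inferential results are underpowered, does not address this, because a larger sample would leave the null just as true.

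**Working it through.** **Inputs from the protocol article**
- 19 men per arm (Sample Size). The plan's own figure reproduces: 15 / (1 − 0.20) = 18.75, rounded up to 19 per arm, 38 in total.
- Seven scales measured at week 0 (Table 1): Berg Balance Scale, Timed Up and Go, Functional Reach Test, Short Physical Performance Battery, Fall Efficacy Scale–International, Geriatric Depression Scale and EQ-5D-5L.

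**Assumptions**
- Two-sided 5% level, because none is stated for the baseline tests.
- Sound allocation and roughly normal data.
- Correlation between scales of 0 to 0.5.
- Proportions of 0.3 to 0.5 for categorical variables.

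**1. False alarms from the t tests.** For seven independent tests with no true difference:

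1 − (1 − 0.05)^7 = 0.302

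A simulation of 20,000 trials of 38 men gives 0.295 with uncorrelated scales, 0.273 at a correlation of 0.3, and 0.232 at 0.5. The range is therefore about 23% to 30%. The number of further baseline variables is not given, so they are not counted.

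**2. False alarms from the Fisher tests.** Exact enumeration over all pairs of counts with 19 per arm and equal proportions gives a true size of 0.024 at a proportion of 0.3 and 0.028 at 0.5. These tests raise fewer false alarms than their nominal 5%.

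**3. How large an imbalance must be to be flagged.** The standard error of a mean difference in SD units is √(2/19) = 0.324. The smallest significant observed difference is

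t(0.975, 36 df) × √(2/19) = 2.028 × 0.324 = 0.658 SD.

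An observed imbalance of 0.5 SD gives t = 0.5 / 0.324 = 1.54 and p = 0.13, so it is not flagged.

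**4. How often a sizeable imbalance goes unflagged.** Chance alone gives an imbalance of at least 0.5 SD with probability

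2 × [1 − Φ(0.5 / 0.324)] = 0.123.

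In 100,000 simulated randomisations with 19 per arm, 60.4% of these were non-significant. Hence 0.123 × 0.604 = 0.074, or about 7% of randomisations per variable. The rest of the 12% would be flagged and should not be counted as missed.

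**The case against.** The strongest reply is that nothing depends on these tests. The article says only that the groups will be compared. It does not choose covariates or models from the p-values, or make any claim of comparability conditional on them. The trial also says that it does not assess effectiveness, that between-group differences are not a key objective, and that inferential findings will be read with caution. All of this stands, and it limits the point to how results may be described. It does not make the tests informative.

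Three stronger readings are tempting, and the document supports none of them.

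- **That the tests lead to distorted outcome differences.** With an assumed baseline to follow-up correlation of 0.5 to 0.9, a 0.5 SD imbalance moves the unadjusted follow-up difference by correlation × 0.5 = 0.25 to 0.45 SD. It moves the change-score difference by (correlation − 1) × 0.5, which is 0.25 down to 0.05 SD in the opposite direction. But the unadjusted differences are to be reported whatever the baseline tests show. The shift is the same with or without the tests, so they do not cause it and deleting them does not cure it. Over repeated randomisations the unadjusted difference is unbiased, and its confidence interval already allows for chance imbalance.
- **That the tests have low power for a true baseline difference.** Under sound random allocation there is no true difference to detect, so power has no meaning here.
- **That t tests are imposed on skewed scales.** The same section says that distributions will be explored and that other models will be used for non-normal data.

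**Conclusion.** The point holds as a minor one. The article states an analysis that cannot inform the question of balance, and this is not a detail left to a fuller plan. The chance of at least one spurious significant t test over the seven scales is about 23% to 30%. Imbalances up to about 0.66 SD go unflagged, and unflagged imbalances of at least 0.5 SD occur in about 7% of randomisations per variable. The Fisher tests are conservative, at about 2.4% to 2.8%.

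These figures rest on 19 men per arm, an assumed two-sided 5% level, approximate normality and the assumed correlations and proportions. The argument that the null is true rests on allocation having been sound. The consequence is limited to misleading statements about comparability or about the randomisation. No estimate, confidence interval, sample size or feasibility outcome changes because of these tests.

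**What to change.** In the Statistical Analysis section:

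1. Delete the baseline t tests, the Fisher exact tests and their p-values.
2. Report baseline characteristics by arm descriptively: mean and SD, median and IQR, or number and percentage.
3. Describe any imbalance by its size (in SD units for scales) and by how strongly the variable is expected to predict outcome.
4. State that no choice of covariate or model, and no claim of comparability, depends on a baseline p-value.
5. As a separate step for chance imbalance in the outcomes, adjust each outcome comparison for its own baseline value (for example by ANCOVA), whatever imbalance is observed.

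Items 1 to 4 are wording only and mean fewer analyses. Item 5 adds a model but uses baseline values already collected. The sample size stays at 38. The article describes the analysis as under way, so the final report should apply the change and say that it departs from the published plan.
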